### Outcome Measures

#### Primary Outcome

In this study, the primary outcome will be graded according to the CCS classification (Sangareddi et al., 2004). We will compare the difference between the two groups in the proportion of subjects whose CCS classification decreased ≥1 after 12 weeks of medication.

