### Sample Size Calculation

In this study, the sample size is determined by the proportion of subjects whose CCS classification decreased ≥1 after 12 weeks of medication. According to the results of our clinical trials (unpublished data) and our clinical experience, after a 12 weeks intervention, we assume the proportion of subjects whose CCS classification will decrease by ≥ 1 will be 85% in the treatment group and 70% in the placebo control group. Given a type I error rate of *α* = 0.025, a power of 80% (type II error rate of *β* = 0.2), and considering of 20% possible dropout rate, 236 patients should be allocated to the treatment group and 118 patients in the placebo group. For the convenience of randomization, the final sample size was set at 240 cases in the treatment group and 120 cases in the placebo group.

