### Statistical Analysis

The statistical analysis plan will be specified before the final data analyses. The statistical analyses will be undertaken via Statistical Analysis System 9.4 (SAS Institute, Inc. Cary, NC) by the Department of Medical Statistics, at the National Center for Cardiovascular Diseases, Beijing. Data from all patients who undergo randomization will analyzed according to the intention-to-treat (ITT) principle. Consistent with the CONSORT statement and ITT principle, the last observation carried forward method will be used for missing values.

For quantitative data, we will calculate the mean, standard deviation, median, minimum, maximum, and interquartile range. For qualitative data, we will describe various frequencies or percentages. The student’s t-test will be used for quantitative data with normal distribution, while the Wilcoxon rank sum test will be used for quantitative data without normal distribution. The chi-square test or Fisher’s exact test will be used for qualitative data. We will analyze intra-group or inter-group differences before and after treatment. Concerning primary outcome, the effectiveness rate of patients whose CCS classification decreased ≥1 after 12 weeks of medication, the differences intra-group or inter-group will be compared using the CMH chi-square test adjusted for clinical site. We will include sex, center, baseline CCS classification, baseline HbA1c level, and baseline lipid levels as covariates in an analysis of covariance (ANCOVA) for statistical differences between groups by reducing the error variance. Statistical Significance will be assumed at a two-sided p-value less than 5%. The relative risk with corresponding 95% confidence interval (CI) to compare dichotomous variables will be calculated.

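### The site-stratified CMH test is also assigned to within-arm differences in the primary responder rate, where there is nothing to compare, and no clearly paired test is named for the other before/after analyses

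*Protocol article*

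**What the plan says.** The Primary Outcome section defines a between-arm comparison of responders: "We will compare the difference between the two groups in the proportion of subjects whose CCS classification decreased ≥1 after 12 weeks of medication".

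The Statistical Analysis section goes further. For outcomes in general it states: "We will analyze intra-group or inter-group differences before and after treatment". For the primary responder rate it states: "the differences intra-group or inter-group will be compared using the CMH chi-square test adjusted for clinical site".

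The other tests named in that section are Student's t ("t-test will be used for quantitative data with normal distribution"), the rank sum test ("Wilcoxon rank sum test will be used for quantitative data without normal distribution"), and chi-square or Fisher's test ("exact test will be used for qualitative data"). Signed-rank, McNemar and an explicitly paired t-test do not appear.

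The Sample Size Calculation section assumes that the responder proportion "will be 85% in the treatment group and 70% in the placebo control group". The Inclusion Criteria require CCS class II or worse at screening, and the Intervention section gives every participant standard treatment.

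**The concern.** Two things are at issue.

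- **Validity.** A CMH test stratified by site compares independent groups within each site. Within one arm, the responder rate supplies no second group. For the other outcomes, comparing the same patients before and after treatment needs a paired method, and the list of tests does not clearly contain one.
- **Interpretation.** Even a correctly paired within-arm test mixes any drug effect with background therapy, placebo response and regression to the mean after selection on CCS class. The plan itself expects most placebo patients to improve. A p-value for improvement within the TJC (active) arm would therefore say little about TJC, yet it could be reported beside the between-arm result under the same 5% threshold.

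**Working it through.** **1. The plan's own figure.** Inputs from Sample Size Calculation: 85% v 70%, allocation 2:1, alpha 0.025 (read as one-sided, equivalent to two-sided 0.05), power 80%, dropout 20%. With unpooled variance:

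n(control) = (1.960 + 0.842)² × (0.70×0.30 + 0.85×0.15/2) / 0.15² = 7.849 × 0.27375 / 0.0225 = 95.5

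Dividing by 0.8 gives 119.4, against the stated 118, a difference of about 1%. The sample size therefore rests on the between-arm contrast. Power for that contrast at two-sided 0.05 is about 90% with 240/120 patients and about 83% with 192/96 completers. Nothing below changes these figures.

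**2. Within-arm CMH on the responder rate.** Responder means that CCS class at week 12 is at least one lower than at baseline. At baseline the change is zero for everyone, so the baseline rate is 0/n in every site. Take 96 placebo completers (120 × 0.8), of whom 0.70 × 96 ≈ 67 respond. Treating 0/96 and 67/96 as independent samples gives

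chi-square = 192 × (96×67)² / (96 × 96 × 67 × 125) = 192 × 67/125 = 102.9, p ≈ 3.5×10⁻²⁴

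The result is empty, because the zero is built into the definition. If the phrase instead means CCS class at baseline against CCS class at week 12, there is a before and an after, but site strata still do not match each patient with himself or herself.

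**3. What a valid within-arm test would show on placebo.** The illustration is a two-sided exact sign test of improved against worsened, with unchanged patients dropped. The 70% rate comes from the plan. The share who worsen is not given, so it is varied.

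| Placebo patients | Improve | Worsen | p |
|---|---|---|---|
| 96 | 67 | 29 (all the rest) | 0.00013 |
| 96 | 67 | 14 (15%) | 1.9×10⁻⁹ |
| 96 | 67 | 0 | 1.4×10⁻²⁰ |
| 120 | 84 | 36 (all the rest) | 0.000014 |
| 120 | 84 | 0 | 1.0×10⁻²⁵ |

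In the most adverse case the test rejects at 59 or more improvers of 96. At a true rate of 70% that has probability 97.2%. With 120 patients the cut-off is 72 and the probability 99.3%.

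**4. Independent-sample tests on paired continuous data.** With equal SDs and correlation r between baseline and week 12 (assumed; the protocol gives none), the variance of the mean change is 2σ²(1−r)/n when paired and 2σ²/n when pairing is ignored. The interval is too wide by a factor 1/√(1−r): 1.41 at r = 0.5, 1.58 at r = 0.6, 1.83 at r = 0.7. Simulation with n = 96 and 20,000 repetitions, nominal size 5%:

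| r | True size, unpaired t | Power for 0.2 SD, unpaired | Power for 0.2 SD, paired |
|---|---|---|---|
| 0.3 | 2.0% | 25% | 38% |
| 0.5 | 0.6% | 21% | 50% |
| 0.7 | 0.04% | 15% | 72% |

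**The case against.** The strongest reply is that efficacy is inferred between arms throughout. The study hypothesis is superiority to placebo, the Primary Outcome section compares the two groups, the sample size rests on 85% v 70%, and the covariate-adjusted analysis is for differences between groups. A reader might infer from the within-arm wording that these tests are planned as evidence of efficacy. The documents do not say so, and no section lets a within-arm p-value decide anything. That stands.

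It is also fair that, for outcomes other than the primary, no test is expressly assigned to the within-arm analyses. Student's t has a paired form, and a later analysis plan may name the others. That unpaired tests will be used there is an inference from the list. It is a reasonable one, because rank sum, chi-square and Fisher's exact are independent-sample tests, but it remains an inference.

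Neither reply rescues the primary-outcome sentence. It assigns a specific test to a specific within-arm use, and that use has no valid meaning. An analysis plan not yet seen does not cure a rule that is stated and wrong.

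**Conclusion.** The point holds, with limited reach. Assigning a site-stratified CMH test to within-arm differences in the responder rate is wrong as written. For the remaining outcomes, within-arm analysis is planned without any clearly paired test.

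Two stronger readings are not supported:

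- **That a within-arm test is certain to be significant on placebo.** The very small p-values (about 10⁻²⁵) need all 120 placebo patients analysed and none worsening. What can be said is about 97% or more, for CCS class only, under the plan's assumed 70% placebo response and with 96 completers. The documents give no comparable figures for treadmill, glucose, lipid, nitroglycerin or angina-questionnaire outcomes.
- **That ignoring the pairing would create false positives.** With positive correlation the effect is the reverse: intervals about 1.4 to 1.8 times too wide at assumed r of 0.5 to 0.7, and reduced power.

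The between-arm primary test, its significance level and the sample size are untouched. What is at risk is the reporting of an undefined or non-discriminating within-arm p-value as if it informed efficacy.

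**What to change.** In the Statistical Analysis section, or in the analysis plan that it says will be specified before the final analyses:

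1. Apply the site-stratified CMH test to the between-arm comparison of the responder rate only, and remove the within-arm use.
2. State that efficacy conclusions rest only on between-arm contrasts, for the primary and secondary outcomes alike.
3. Report within-arm change descriptively. If any within-arm interval or test is kept, name a paired method suited to the data (paired t, signed-rank or McNemar) and label it descriptive. The label matters even for intervals: under the plan's placebo assumption, an interval for CCS improvement on placebo would very probably exclude no change as well.

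The cost is wording. Sample size, visits and data collection do not change.

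### An ANCOVA with no stated outcome or rank follows the CMH test for the binary primary, leaving open whether a linear equal-variance model also applies to a yes/no endpoint and which analysis decides

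*Protocol article*

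**What the plan says.** All of this is in the protocol article.

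- **Primary Outcome:** the endpoint is binary. The groups are compared on "the proportion of subjects whose CCS classification decreased ≥1 after 12 weeks of medication".
- **Statistical Analysis, test of the primary:** differences in this rate "will be compared using the CMH chi-square test adjusted for clinical site". Site is the only adjustment factor named.
- **Statistical Analysis, next sentence:** "We will include sex, center, baseline CCS classification, baseline HbA1c level, and baseline lipid levels as covariates in an analysis of covariance (ANCOVA"). The stated purpose is "for statistical differences between groups by reducing the error variance". No outcome is named, and the analysis is not called primary, supportive or secondary.
- **Statistical Analysis, effect measure:** "The relative risk with corresponding 95% confidence interval (CI) to compare dichotomous variables will be calculated".
- **Statistical Analysis, quantitative data:** Student's t-test, or the Wilcoxon rank sum test if the data are not normal.
- **Statistical Analysis, level:** "Statistical Significance will be assumed at a two-sided p-value less than 5" per cent.

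No regression model for a binary outcome is named anywhere in the article.

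**The concern.** The ANCOVA sentence directly follows the primary-outcome sentence and introduces no new subject. Its covariates include baseline CCS class, which is the baseline of the primary. They omit the baselines of the treadmill measures, the Seattle angina questionnaire, nitroglycerin use and fasting glucose. Quantitative outcomes already have their own tests. A reader going through the section in order could therefore take the ANCOVA as a second, adjusted analysis of the responder rate.

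Two things are at stake on that reading. First, ANCOVA assumes one residual variance for both arms. A yes/no outcome has variance p(1−p), which differs between arms when the rates differ, and under 2:1 allocation that difference does not cancel. Second, the primary would have two between-group analyses with different adjustment sets and no statement of which one decides.

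On the other reading, with ANCOVA for continuous outcomes only, the primary is not adjusted for baseline CCS although the plan itself lists it as a covariate. The ANCOVA then overlaps, unranked, with the t-test/Wilcoxon rule. The sentence needs rewriting on either reading.

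**Working it through.** **Inputs from the article.** The assumed rates "will be 85% in the treatment group and 70% in the placebo control group", 2:1 allocation, 240 and 120 patients, 80% power and 20% dropout come from Sample Size Calculation. That section gives α = 0.025 without stating sidedness; Statistical Analysis gives two-sided 5%.

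**1. The plan's own figure.** With one-sided 0.025 (the same as two-sided 0.05) and unpooled variances:

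n(placebo) = (1.960 + 0.842)² × (0.70×0.30 + 0.85×0.15/2) / 0.15² = 7.849 × 0.27375 / 0.0225 = 95.5

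Dividing by 0.8 for dropout gives 119.4 placebo and 238.7 treatment, against the stated 118 and 236. That is close (about 1% apart), so the rates and allocation can be used below.

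**2. Interval if ANCOVA is applied to the primary.**

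- Arm variances: 0.85×0.15 = 0.1275 (TJC); 0.70×0.30 = 0.21 (placebo). The smaller arm has the larger variance.
- True SE of the difference: √(0.1275/240 + 0.21/120) = √0.00228125 = 0.0478.
- Equal-variance SE: pooled variance (240×0.1275 + 120×0.21)/360 = 0.155; √(0.155 × (1/240 + 1/120)) = 0.0440. Dividing by 358 instead of 360 gives 0.0441.
- Ratio 0.0440/0.0478 = 0.922. The half-width is 8.6 percentage points where 9.4 is correct.
- Coverage: 2Φ(1.96 × 0.922) − 1 = 0.929.

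After 20% dropout (192:96) the ratio and coverage are the same. At 1:1 the ratio is 1.000, so the shortfall comes from the 2:1 allocation combined with unequal rates. When the rates are equal the arm variances are equal, and the problem disappears.

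**3. Simulation.** There were 4,000 trials per scenario. The following are assumptions that the article does not give: five sites of equal expected size with no site effect; baseline CCS II/III/IV at 60/30/10%; a CCS odds ratio of 1, 2 or 3 per class; the other covariates non-prognostic. Ranges are over the three odds ratios, and over both sample sizes where marked *.

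| Quantity | Result |
|---|---|
| ANCOVA 95% CI coverage, 85% v 70%* | 92.4–93.3% |
| Same model, robust variance* | 94.5–95.1% |
| Type I error at 70% v 70%, ANCOVA | 4.4–5.6% |
| Type I error at 70% v 70%, site CMH | 4.6–5.4% |
| Power at 240:120, site CMH | 89.4–91.3% |
| Power at 240:120, site + baseline-CCS CMH | 88.7–91.8% |
| Site CMH and ANCOVA disagree on significance, 85% v 70%* | 2.1–4.7% |

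The Monte Carlo standard error at a true 5% is √(0.05×0.95/4000) = 0.34 percentage points, so both type I error ranges are compatible with 5%. Over both sample sizes, adding baseline CCS to the CMH changed power by between −1.5 and +1.2 points.

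**4. Size of the open choice.** Suppose success were claimed when either test was significant. The false-positive rate would be (rate A + rate B + disagreement)/2. With no effect this gives (5.6+5.4+1.4)/2 = 6.2%, (4.4+4.6+2.0)/2 = 5.5% and (4.7+5.0+2.9)/2 = 6.3% for odds ratios 1, 2 and 3. The article does not plan such a choice; it only fails to rule it out.

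**The case against.** The article never says that the ANCOVA is for the primary. CMH is the only method expressly tied to that outcome. Baseline HbA1c and lipids are baselines of continuous secondary outcomes, and reducing error variance is the language of continuous data. The interval named for dichotomous variables is the relative-risk interval, so an ANCOVA risk-difference interval might never be reported. The ranking of supportive models is often left to the SAP, which the article says will be specified before the final analyses.

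Most of this stands, and it limits the point. A reader might infer that the plan prescribes ANCOVA for the primary; the text supports only that it leaves this open. A reader might infer two declared primary analyses; there is one declared test and one unassigned model. A reader might infer a raised false-positive rate from ANCOVA itself; the rate stays near 5%. A reader might call the omission of baseline CCS from the CMH an error; under randomisation the site-stratified test is valid without it, and the power difference is small in either direction.

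The objection does not remove the ambiguity. The article chose to state an adjusted model, placed it immediately after the primary test with the primary's own baseline as a covariate, and gave it no outcome or rank. That is stated text fixed badly, not detail deferred to another document.

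**Conclusion.** The point holds as an unassigned and unranked model beside a binary primary. If the ANCOVA is applied to the primary, its risk-difference interval is about 8% too narrow (coverage about 93%) at 85% v 70% and 2:1, with no type I error inflation of that test. It would then be a second analysis that disagrees with the CMH on significance in about 2–5% of trials when the effect is real. If ANCOVA is for continuous outcomes only, what remains is an inconsistency: baseline CCS is a listed covariate, but the primary is not adjusted for it.

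The interval result rests on the plan's own rates and allocation. The power and disagreement figures also rest on the assumed site sizes, CCS mix and prognostic strength. Severity is moderate.

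**What to change.** Reword Statistical Analysis, and carry the same wording into the SAP before unblinding:

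1. The site-stratified CMH test is the single confirmatory analysis of the primary. Adding baseline CCS class as a stratum is optional. The relative risk and its 95% CI come from the same stratified analysis.
2. ANCOVA applies to continuous outcomes only, each adjusted for its own baseline value. State how it ranks against the t-test and Wilcoxon test.
3. If covariate adjustment of the primary is wanted, name a binary-outcome model as supportive. One example is logistic regression on treatment, site, baseline CCS, sex, HbA1c and lipids, reported as a standardised risk difference or relative risk with a robust standard error.

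The cost is wording only. Table 1 already schedules demographics, CCS class, HbA1c and lipids at Visit 1, and the sample size does not change.

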### Current Status

Patient recruitment for the trial began in October 2020. The relevant protocol was registered at http://www.chictr.org.cn on August 28, 2020. The trial registration number is ChiCTR2000037491.

## Discussion

The diabetic environment promotes the development of CHD through multiple mechanisms, which include glycolipid metabolic disorders, oxidative stress, and increased inflammatory cytokine production (Yahagi et al., 2017). As a Chinese patent medicine, TCJ has been widely used in China as a component of T2DM treatment. Clinical studies have shown that TJC has a significant effect on glycolipid metabolism and diabetes vascular-related complications. Clinical findings have also demonstrated that fasting blood glucose (FPG), 2 h postprandial blood glucose (2-h PBG), HbA1c, TG, TC, and LDL-C levels in TJC group were significantly lower than those of placebo group (Eremire et al., 2019). Moreover, TJC can enhance the immune function and reduce the inflammatory response as shown by analyzing the immune inflammation indicators and had no obvious toxic and side effects on T2DM patients (Eremire et al., 2019). Yang et al. 2016 established a diabetic STZ-induced rat model to investigate the effects of TJC on diabetic neurovascular complications and confirmed that TCJ could improve the footprint gait parameters, nerve conduction velocity, and peripheral nerve pathological injury (Yang et al., 2016).

The representative active ingredients in TJC include calycosin7-O-β-D-glucopyranoside, ononin, formononetin, heterophyllin B, and gypenoside (Yang and Wang, 2020). Experimental studies have demonstrated that calycosin7-O-β-D-glucopyranoside, ononin, formononetin, and gypenoside can significantly decrease blood glucose and lipid levels, which contribute to release lipid metabolism disorder and can effectively remove reactive oxygen species and alleviate oxidative damage (Müller et al., 2012; Sham et al., 2017; Liu et al., 2019). As an effective component of TJC, formononetin can significantly reduce the expression of inflammatory factors such as tumor necrosis factor-α and interleukin-1β (Gu et al., 2014). Heterophyllin B inhibited the lipopolysaccharide-induced inflammation and apoptosis through the phosphoinositide 3-kinase/protein kinase B signaling pathways and has been proposed as a potential therapeutic target for the treatment of inflammatory diseases (Yang et al., 2018). Gypenosides can improve diabetic cardiomyopathy and CHD by inhibiting reactive oxygen species-mediated NLRP3 inflammasome activation (Lee et al., 2013; Zhang et al., 2018b). Thus, cumulative studies to date have evaluated the benefits of TJC in improving glycolipid metabolism, oxidative stress, and inflammatory responses. In addition, our previous studies have shown TJC can uniquely improving the exercise tolerance in T2DM-CHD. However, there have been no relevant randomized controlled trials conducted to date, and we believe that our study will contribute to a better understanding on the efficacy of TJC in T2DM-CHD.

Several limitations need to be considered, however. First, this study will not recorded intervene on patients' diet and exercise, which may have an impact on the level of glucose and lipid, and cardiovascular events (Ades, 2001). Second, AEs will only be recorded and processed during the 3 months intervention period, which is a relatively short period, but the short-term results could encourage further prospective studies with different treatment regimens and longer follow-up. Finally, even in multicenter trials, measurement errors from laboratory testing and individual differences in the process of CCS classification are inevitable, which may possibly lead to different efficacies of TJC. More effort should be made to optimize the deficiencies and answer these questions in future studies.

## Conclusion

This study will investigate the therapeutic potential of TJC as a combination drug. The results of the study will provide reliable clinical research evidence for the application of TJC in improving cardiac function and exercise tolerance in T2DM-CHD patients.

## Data Availability

The original contributions presented in the study are included in the article/Supplementary Material, further inquiries can be directed to the corresponding authors. After the completion of the study, the data and results of the trial will be disseminated to the general public through scientific conferences, presentations, and open-access medical journals.
